In 2014, the CM/CC program was available to commercially insured individuals across lines of business. Approximately 30,000 members participated in the program in 2014. The current study was designed to determine the following:

**Objective 1:** if the CM/CC program would statistically significantly impact health outcomes for commercial members identified as being high-need, high-cost (the QIS is powered to answer this primary objective), and

**Objective 2:** if the addition of a Community Health Worker to the care team would substantially impact health outcomes for Individual Public Exchange members identified as being high-need, high-cost (the QIS is not powered to answer this secondary objective).

It is important to note that throughout the study period, the CM/CC program will continue to be available to all commercial health plan members similar to previous years, including the control group in the current QIS, who are 1) discharged from an inpatient facility and identified as being at high risk for readmission and 2) identified via physician referral or self-referral as someone who may benefit from care coordination.

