## IV. a. 2. Justification of Study Design

IV. a. 2. Justification for a pragmatic design: Pragmatic, or naturalistic designs, are designed to evaluate how a technology works in normal or usual practice and take into account patient and provider variations and can range from experimental to quasi-experimental studies. Pragmatic experimental designs retain random allocation to treatments to minimize bias, but offer fewer restrictions in how patients are recruited and followed after randomization, thus increasing external validity and generalizability. Pragmatic experimental designs have been used previously to evaluate strategies to promote the adoption of low-risk public health recommendations, such as CMS's evaluation of the Health Support pilot (i.e., Chronic Care Improvement Program) or the National Health Service's (NHS) evaluation of the impact of fecal occult blood test (FOBT) screening for colorectal cancer.

Generally, experimental designs are structured so that recruitment precedes randomization in order to evaluate the efficacy of an intervention; however, randomization occurs before recruitment (i.e., enrollment) in pragmatic methodologies which are designed to evaluate the effectiveness of an intervention. The use of the pragmatic design balances the goals of internal and external validity.

IV. a. 3. Sample Size: The study was powered for acute inpatient admissions, the most restrictive outcome, using the sample size estimation for trials of recurrent events in SAS. A baseline study of patients meeting the high-need, high-cost criteria suggests that a total sample size of 171,454 (85,727 per treatment arm) would provide the study with  $\geq 80\%$  power to detect the following intent to treat differences between treatment groups at an  $\alpha=0.05$  over the first 12 months of the four year study:

- a 2.5% reduction in acute inpatient admissions
- a 2.5% reduction in 30-day all-cause readmissions
- a 2.5% reduction in emergency room visits
- a 2.5% increase in primary care physician visits
- a 2.5% increase in specialist physician visits

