Given a treatment effect of a 20% reduction in utilization for the as-treated population, an average of 10.6 months of at-risk exposure, an estimated program engagement rate of 20% of the qualified population with an average of 6.5 months of engagement in the program, a sample size of 85,727 individuals in the program treatment arm was used to power the most restrictive outcome (i.e., acute inpatient admissions) using preliminary data. In other words, the study's original planned sample size of approximately 200,000 members for the initial 12-month period, including both treatment arms, was sufficient to allow decision makers to assess if the CM/CC intervention could improve the targeted outcomes in the qualified population by year. The larger

cumulative sample sizes, included in years 2-4 of the study also address the salient business need for continuous quality improvement – the foundation of a QIS.

IV. a. 4. Rationale for the study endpoint: The study endpoint is defined as documentation of utilization including acute inpatient admissions, 30-day all-cause re-admissions, outpatient emergency room (ER) visits, primary care physician (PCP) visits, and specialist physician visits using administrative claims data. These outcome measures align with National Committee on Quality Assurance's (NCQA) Healthcare Effectiveness Data and Information Set (HEDIS) quality measures, Centers for Medicare & Medicaid Services' (CMS) Five Star Quality Rating System for Medicare Advantage Plans, and prior analysis of the effectiveness of care coordination and case management programs, represent significant costs and indicators of complications as well as represent important factors needing additional research as it relates to the care of patients.

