#### **IV. b. Data Analysis and Data Monitoring**

*Primary Data Analysis:* All analyses will be based on administrative data. In order to address claims lag, the administrative data will be pulled four months following the end of each intervention period.

Univariate analyses (standardized differences) will be used to test for baseline differences between the treatment groups. Any statistically significant differences in baseline characteristics will be controlled for in the multivariable models assessing the study outcomes. Unless otherwise noted, all tests will be two-sided tests with  $\alpha = 0.05$ . Model diagnostics will be utilized to evaluate the need to address outliers.

The primary study outcomes include the following:

- a 2.5% reduction in acute inpatient admissions
- a 2.5% reduction in 30-day all-cause readmissions
- a 2.5% reduction in emergency room visits
- a 2.5% increase in primary care physician visits
- a 2.5% increase in specialist physician visits

Utilization metrics will be compared between intervention groups at 12, 24, 36 and 48 months following randomization using a repeated measures Poisson or negative binomial regression model. Zero-inflated models will be utilized if appropriate. The Cox proportional hazards test will be used for all cause 30-day readmission. Results will be reported in aggregate, as well as stratified by year of randomization.

*Secondary Data Analyses:* The study will also explore numerous secondary outcomes that were not powered, but that are important for continuous quality improvement – the primary goal of a QIS. Examples include the following:

- Total cost of care: Utilization and cost will be evaluated for all service categories to identify hypotheses for continuous quality improvement.
- Variable cohort definitions:
  - A “once qualified, always qualified” definition will be used to evaluate the long-term impacts of the program after a member is no longer identified by the monthly refresh of the algorithms. This mirrors a more academic approach to the measurement of outcomes.
  - An “operational” definition will include members until 120 days after they are no longer actively identified by the monthly refresh of the algorithms. This view is designed to drive continuous quality improvement.
- Health plan type: The impact of the program among the Individual Exchange population compared to the traditional Fully Insured population will be evaluated.

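### Five primary outcomes, each tested at two-sided 0.05 at four time points, with no rule on which result decides Objective 1

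*Protocol*

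**What the plan says.** Section IV.b, Primary Data Analysis, sets one significance rule for everything: "Unless otherwise noted, all tests will be two-sided tests with" alpha 0.05. No exception is noted later. The next paragraph opens with "The primary study outcomes include the following" and lists five: acute inpatient admissions, 30-day all-cause readmissions, emergency room visits, primary care visits and specialist visits. Then: "Utilization metrics will be compared between intervention groups at 12, 24, 36 and 48 months following randomization", using a repeated measures count model, with a Cox model for readmissions. The section adds "Results will be reported in aggregate, as well as stratified by year of randomization".

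Objective 1 in section II.b asks "if the CM/CC program would statistically significantly impact health outcomes for commercial members identified as being high-need, high-cost". The hypothesis in section IV.a.1 is written for utilization rates in general and names no single outcome.

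Section IV.a.3 (Sample Size) claims at least 80% power at alpha 0.05 for a 2.5% difference on each of the five outcomes over the first 12 months. It uses admissions for the calculation because that outcome is the most demanding. It expects decision makers to judge whether the programme could "improve the targeted outcomes in the qualified population by year".

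**The concern.** With five primary outcomes, an alpha of 0.05 per test is the error rate of the primary conclusion only if the plan says how the five combine: one decides, all must succeed, or the alpha is shared. The protocol says none of these. It gives no order, no split of alpha and no adjustment for repeated comparisons over time. This is more than silence that an analysis plan could fill, because the protocol itself fixes 0.05 for every test.

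Section I expects positive results to lead to expansion of the programme to the whole high-need, high-cost population. Without a deciding test, one favourable result among several could be presented as meeting Objective 1, at a false-positive rate above the stated one.

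**Working it through.** **The plan's own figure.** The only error rate stated is 0.05 per test; none is given for Objective 1 as a whole. The total of 171,454 cannot be reproduced, because the baseline admission rate and the dispersion are not given. The point does not depend on it.

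**Inputs from the protocol.** Five primary outcomes, two-sided 0.05 and four time points (section IV.b). Accrual is monthly (section IV.a.7) over four years (section I), and the intervention ends on 10/31/2019 (timeline, section IV.b).

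**Assumptions.** Any one significant primary result counts as an impact. The five test statistics share a common correlation rho. Results at successive time points are cumulative, with correlation √(t_i/t_j) for information fractions t_i < t_j.

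**One time point.** For independent outcomes:
- two-sided: 1 − 0.95⁵ = 0.226;
- favourable direction only: 1 − 0.975⁵ = 0.119.

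Whatever the correlation, the rates cannot exceed 5 × 0.05 = 0.25 and 5 × 0.025 = 0.125.

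**Four time points.** Two spacings were simulated (1,000,000 draws each, |z| > 1.96):
- *Equal:* t = 0.25, 0.50, 0.75, 1.
- *Front-loaded:* uniform entry over 48 months, with follow-up ending when the intervention ends. The share of person-time within the first m months of follow-up is (m − m²/96)/24, which gives 0.44, 0.75, 0.94 and 1.

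Chance of at least one false significant primary result, two-sided / favourable only:

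| | rho 0 | rho 0.5 | rho 0.8 |
|---|---|---|---|
| Five outcomes, one time point | 23% / 12% | 18% / 9% | 13% / 6% |
| Five outcomes, four time points, equal | 49% / 28% | 41% / 21% | 29% / 15% |
| Five outcomes, four time points, front-loaded | 43% / 24% | 35% / 18% | 25% / 13% |

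For comparison, one outcome at four equally spaced time points gives 12.6% two-sided.

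**Not counted.** The strata by year of randomization and the monthly outcome reports are left out. Cumulative looks by calendar year under the same uniform entry (information proportional to 1, 4, 9, 16) would give more: 47–56% two-sided for rho 0.5 to 0. The protocol's wording is time since randomization, so that case is not used for the range.

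**Cost of an equal split.** Exactly 80% power at 0.05 corresponds to a standardized effect of 1.9600 + 0.8416 = 2.8016. At 0.01 the critical value is 2.5758, so power is Φ(2.8016 − 2.5758) = 0.59. Restoring 80% needs (2.5758 + 0.8416)² / 2.8016² = 1.488 times the sample: 171,454 × 1.488 ≈ 255,000 members.

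**The case against.** The protocol nowhere says that any one significant result suffices. Objective 1 speaks of outcomes in the plural, and a rule that all five must succeed would not inflate the error at all. The comparison at four times may be member follow-up within one repeated measures model, not four separate occasions to claim success. The readmission model has less explicit timing. Expansion would follow only favourable results, so the two-sided rate overstates that risk about twofold. Success rules are often left to an analysis plan, and admissions in the first 12 months already anchor the sample size.

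Much of this stands. A reader might infer that the plan carries a false-positive rate of 41–49%. The documents do not support that as a fixed property: it requires any-one-counts, correlation of at most 0.5 and equally spaced cumulative looks, and it counts harmful as well as favourable results. A reader might also infer that only admissions were powered, but section IV.a.3 claims power for all five.

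The objection does not remove the point. No all-must-succeed rule is written. Using admissions for sizing does not make it the deciding outcome, since section IV.b lists it as one of five. Section IV.a.3 expects assessment year by year. If each outcome had only one test over all four years, the one-time-point rates would still apply. The exploratory label in section IV.b covers the secondary outcomes, while the primary objective is declared powered.

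**Conclusion.** The concern holds as a missing decision rule combined with a fixed alpha of 0.05 for every test. If any one significant primary result counts, the error rate at a single time point is 13–23% two-sided (rho 0.8 to 0), or 6–12% in the favourable direction against a nominal 2.5%. That part needs no assumption about looks and is the firmer figure. Four time points raise it to roughly 25–49% two-sided, or 13–28% favourable. That range is a set of scenarios, because the protocol gives neither correlation nor information spacing. The common positive correlation is a simplification, most of all for the favourable rate, since visits are meant to rise while admissions fall; the 12.5% bound at one time point holds regardless. The data remain usable. What needs correcting is the claim that can be made from them.

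**What to change.** Amend section IV.b and Objective 1 as follows.

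- Acute inpatient admissions over the first 12 months, the outcome and period used for sizing in section IV.a.3, are the single deciding test for Objective 1, at two-sided 0.05.
- Only if that test is significant are readmissions, emergency room visits, primary care visits and specialist visits tested, by Holm at an overall 0.05. The smallest p-value is then compared with 0.05/4 = 0.0125.
- Results at 24, 36 and 48 months are reported as estimates with confidence intervals, with no separate claims of significance.

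The cost is a change of wording, with no loss of power for admissions. An equal split at 0.01 would instead reduce 80% power to about 59%. The other four outcomes face a stricter threshold and depend on admissions succeeding.

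Timing needs to be disclosed. The timeline scheduled monthly outcome reports from January 2016, and section IV.a.8 already describes 2018 capacity in the past tense, so the choice could follow sight of outcome data. The amendment should state its date and that the choice rests on the original sample-size basis.

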- a. *Challenge the current state via a pragmatic randomized controlled trial with health plan members as the unit of randomization.* Randomly allocate approximately 705,000 high-risk members into two groups over a four-year period. Compare rates of utilization including acute inpatient admissions, readmissions, ER visits, PCP visits, and specialist visits. This knowledge will allow decision makers to minimize uncertainty as they evaluate opportunities to expand the program.
- b. *Investigate the comparative effectiveness of the approaches to improve health outcomes.* The identification of an improved approach to the expansion of the CM/CC program could lead to reduced complications and improved health outcomes.

The long-term aims of the proposed study are to disseminate the study's findings. The authors anticipate that the communication of positive study results would result in the expansion of the CM/CC model to the entire high-need, high-cost population and ultimately, lead to improved health outcomes for members with high costs and utilization.

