### **III. Criteria for Subject Selection**

#### **III.a. Baseline Studies**

**III.b. Number of Subjects:** As of July 2015, there were 4.5 million program eligible members. Among the eligible population 102,014 (point prevalence of 2.28%) were identified via a proprietary administrative algorithm as being high-need, high-cost (i.e., identification in the top five percent of spend and utilization in year 1 and year 2, based on member characteristics in Year 1). Since the inclusion algorithm will be refreshed monthly for 12 months, modelling based on 2014 data suggests that approximately 200,000 unique members will be identified as being at high-need, high-cost, and included in the randomization frame, over the first 12 months of the QIS.

156 **III.c. Gender of the Subjects:** Participants are expected to be 60.1% female.

157  
158 **III.d. Age of the Subjects:** The age range of the sampling frame will be limited to ≥18 years of age.  
159 Participants are expected to have an average age of 47.5.

160  
161 **III. e. Racial and Ethnic Origin:** Racial and Ethnic data are only self-reported for 3.5% of the commercial  
162 population: 20.7% African American, 1.9% American Indian/Alaskan Native, 4.8% Asian, 64.5% White, Non-  
163 Hispanic, 6.6% Hispanic, 0.0% Native Hawaiian or Other Pacific Islander, 1.2% Other, 0.3% Declined to  
164 Answer, and 0.0% Unknown to Member or Uncoded. The distribution of race/ethnicity of the high-need, high-  
165 cost population is expected to mirror the commercial population.

166  
167 **III. f. Inclusion Criteria:** The commercial Fully Insured population members in all states are represented in  
168 the initial population prior to condition identification. This is also inclusive of the Individual Public Exchange  
169 business, part of Health Care Reform, also known as ObamaCare. The age range of the sampling frame will  
170 be 18 or greater years of age. Members must also be actively enrolled in the health plan as of the date of  
171 randomization. Study participants will be identified via proprietary administrative algorithm as being at high-  
172 need, high-cost.

173  
174 **III. g. Exclusion Criteria:** The population sampled will exclude pregnant women, individuals prescribed  
175 medications for infertility, members with evidence of dementing disorders, and members under the age of 18  
176 years old. Members in the following products and plans will also be excluded:

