#### IV. a. 7. Randomization

Eligible participants will be randomly allocated into two groups. The sponsoring organization will own the randomization process. A unique random number will be generated for each member. The members will be randomly allocated each month to each arm. Restriction (e.g., blocking, stratification, matching) will be leveraged as required.

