- Disease: The comparative effectiveness of the program by disease will be evaluated to drive continuous quality improvement and to identify hypotheses for new program offerings. .
- Access to Other Programs: Qualification for other programs will be monitored in order to determine if stratification is necessary by program qualification for other programs since both treatment arms also have access to other care or disease management programs, such as Transplant Resource Services, the End Stage Renal Disease program, the Chronic Kidney Disease program, the Cancer Support program, or the Heart Failure Disease Management program.

*Study Timeline:* The proposed timeline for the QIS includes the following dates & activities:

10/01/2015 IRB Submission  
10/08/2015 Program effective in tech platform  
10/19/2015 Dialer team stages referrals  
11/01/2015 **Intervention begins.** Members start receiving outreach  
12/31/2015 1st monthly operational metrics report available  
01/31/2016 1st monthly operational leading indicator report available  
01/31/2016 1st monthly outcomes report (notifications) available  
05/31/2016 1st monthly outcomes report (claims) available  
06/01/2016 On-site CHW model expanded to 12 states  
12/31/2016 Individual exchange plans end except for NY and VA  
07/01/2017 CHW intervention ends  
10/01/2017 Randomization moved from 50/50 percentage split to 40/60  
09/01/2018 Engagement of inpatient referrals begin  
10/31/2019 **Intervention ends**

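### The allocation ratio changed on 10/01/2017, but the aggregate comparison names no randomisation-cohort or allocation-period term, so as written it is open to bias from differences between early and late entrants

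*Protocol*

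**What the plan says.** Section IV.a.7 (Randomization) sets up monthly cohorts: "The members will be randomly allocated each month to each arm". On design factors it says only "Restriction (e.g., blocking, stratification, matching) will be leveraged as required", and names none.

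The Study Timeline in IV.b records the change of ratio, "10/01/2017 Randomization moved from 50/50 percentage split to 40/60", without saying which arm receives 60%. It also records that most Individual Exchange plans ended on 12/31/2016 and, later, "09/01/2018 Engagement of inpatient referrals begin".

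The Primary Data Analysis paragraph of IV.b names a repeated measures Poisson or negative binomial model for the utilisation counts and a Cox model for 30-day readmission. Comparisons are made at 12, 24, 36 and 48 months after randomisation. On reporting it says "Results will be reported in aggregate, as well as stratified by year of randomization". The only adjustment rule covers baseline characteristics found to differ significantly between arms. Randomisation date, cohort and allocation period are not mentioned, and nothing links the ratio change to the analysis.

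**The concern.** Randomisation makes the arms comparable within a cohort that has one allocation ratio. When cohorts with different ratios are pooled, the arm that receives 60% after the change holds more late entrants than the other arm. Arm then predicts entry period. If entry period also predicts utilisation, the pooled rate ratio differs from 1 even when the programme does nothing.

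The protocol gives reasons to expect the population to change over time. Most Exchange plans leave the source population nine months before the ratio change. Inpatient-risk referrals begin eleven months after it, and those members are selected for risk of the outcome on which the trial is powered. They matter here only if they are pooled into the aggregate, which the protocol does not say.

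The target is a 2.5% reduction, so a bias of one or two percent is large relative to the effect being sought. With about 705,000 members the standard error would be small enough for such a bias to look significant.

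**Working it through.** **The plan's own effect size.** Section IV.a.3 gives a 20% as-treated reduction, 20% engagement, and 6.5 months engaged out of 10.6 at risk. The product is 0.20 × 0.20 × 6.5/10.6 = 2.45%, in line with the stated 2.5%.

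**Inputs from the protocol**
- Total: "Randomly allocate approximately 705,000 high-risk members into two groups over a four-year period" (Purpose of the Study).
- Year 1: "approximately 200,000 unique members will be identified as being at high-need, high-cost" (III.b, Number of Subjects).
- Intervention from 11/01/2015 to 10/31/2019, which is 48 monthly cohorts. The first 23 are allocated 50/50 and the last 25 are allocated 40/60.

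**Assumptions**
- The remaining 505,000 enter evenly over 36 months, 14,028 per month.
- R is the late-to-early ratio of baseline rates. It is not given, so a range is used.
- There is no true effect and no covariate adjustment.

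**Shares of late entrants, counting members**
- Before the change: 200,000 + 11 × 14,028 ≈ 354,306. After: 25 × 14,028 ≈ 350,694.
- Arm receiving 60%: 0.6 × 350,694 / (0.5 × 354,306 + 0.6 × 350,694) = 54.3%.
- Arm receiving 40%: 0.4 × 350,694 / (0.5 × 354,306 + 0.4 × 350,694) = 44.2%.

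**Null rate ratio** (60% arm over 40% arm) = [1 + 0.543(R − 1)] / [1 + 0.442(R − 1)]. If intervention is the 40% arm, take the reciprocal.

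| R | Ratio if 60% to intervention | Ratio if 60% to control |
|---|---|---|
| 0.75 | 0.972 | 1.029 |
| 0.90 | 0.989 | 1.011 |
| 1.00 | 1.000 | 1.000 |
| 1.10 | 1.010 | 0.990 |
| 1.25 | 1.023 | 0.978 |

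A 10% difference therefore gives about 1.0%, and a 25% difference gives 2.2 to 2.9%. A false reduction of the full 2.5% needs R of about 0.78 (60% to intervention) or 1.29 (60% to control).

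**The same, weighted by person-time.** Assume mid-month entry, follow-up to 10/31/2019, no disenrolment and even entry within year 1. Cohort j then contributes 48.5 − j months per member.
- Before: 16,667 × 504 + 14,028 × 335.5 ≈ 13.11 million member-months.
- After: 14,028 × 312.5 ≈ 4.38 million, or 25% of the total.
- Late shares by arm: 0.6 × 4.38 / (0.5 × 13.11 + 0.6 × 4.38) = 28.6%, and 0.4 × 4.38 / (0.5 × 13.11 + 0.4 × 4.38) = 21.1%.
- R = 1.10 or 0.90 gives 1.007 or 0.992. R = 1.25 or 0.75 gives 1.018 or 0.980. The bias is 0.7 to 0.8% and 1.8 to 2.0%.

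**Would it be detected as an effect?** The stated 80% power at 85,727 per arm implies a standard error of −ln(0.975)/(1.960 + 0.842) = 0.0090 for the log rate ratio. Scaled to arms of 387,569 and 317,431 it is about 0.0045. A log bias of 0.0096 to 0.0106 (10% difference, member-weighted) is then rejected about 58 to 66% of the time at a nominal 5%.

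**Year strata**
- Study years 1, 3 and 4 each have one ratio, so the bias is zero.
- Study year 2 (11/2016 to 10/2017) has 11 months at 50/50 and one at 40/60. The late shares are 0.6/6.1 = 9.8% and 0.4/5.9 = 6.8%. The ratio is 0.994 at R = 0.8 and 0.992 at R = 0.75.
- Calendar 2017, if used instead, has 9 and 3 months. The late shares are 1.8/6.3 = 28.6% and 1.2/5.7 = 21.1%. The ratio is 0.984 at R = 0.8.

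**After stratification.** Within a stratum of constant ratio and common baseline rate both arms have the same expected rate, so the null ratio is 1.000. If rates differ only between the two periods, before/after strata suffice. Monthly strata also cover drift within them.

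**The case against.** The strongest reply is that IV.b lists no model terms at all. Reporting in aggregate may say only which members are included, and a statistical analysis plan could supply a cohort term. This stands to the extent that the text supports saying no term is named, not that one is ruled out. Even so, the protocol sets the aggregate beside the stratified result and records the ratio change without carrying it into the analysis.

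The adjustment rule also counts. In a trial this large, case-mix differences between arms big enough to matter would often be statistically significant and so adjusted for. The rule can reach only measured characteristics, applies conditionally and does not name randomisation date. It may reduce the bias but cannot be relied on to remove it.

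Follow-up limits the exposure. Members entering after the change have at most 25 months before 10/31/2019. If each comparison uses only members with that much follow-up by then, none reach 36 or 48 months. About 28,056 / 382,361 = 7% of the 24-month set would be late entrants, giving roughly 0.7% bias at a 25% rate difference. The pooled 12-month comparison is the most exposed.

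Inpatient-risk referrals have their own hypothesis (the third null hypothesis in IV.a.1), so they may not be pooled with the rest.

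A reader might infer that the trial's main result is a false treatment effect. The documents do not support that. The power statement in IV.a.3 concerns the first 12 months, when allocation was wholly 50/50, and the protocol does not rank the aggregate above the year-specific results. No period-specific rates are given, and with equal rates the bias is zero.

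**Conclusion.** The point holds as a conditional bias in the aggregate comparison as written. Its existence depends on utilisation differing between members who enter before and after 10/01/2017. The Exchange closures make that plausible, as do the inpatient-risk referrals if they are pooled. Its direction cannot be stated without knowing which arm receives 60%.

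Under the assumed accrual, and before any covariate adjustment, the spurious effect is about 1.0% by members or 0.7 to 0.8% by person-time for a 10% rate difference. For a 25% difference it is 2.2 to 2.9% or 1.8 to 2.0%. It can therefore approach or match the 2.5% target, but only with a rate difference of roughly 20 to 30% and member weighting.

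The powered first-12-month comparison and study-year strata 1, 3 and 4 are not affected. The stratum containing the change keeps about 0.6 to 0.8% for a 20 to 25% rate difference by study year, or about 1.6% at 20% by calendar year. No error in the sample size is implied.

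**What to change.** In IV.b, Primary Data Analysis:
- State that the aggregate model for every outcome, including the Cox model for readmission, is stratified by or adjusted for randomisation cohort. Month is preferable; before/after 10/01/2017 is the minimum.
- Split the year stratum that contains 10/01/2017 at that date, and say whether year means study year or calendar year.
- State in IV.a.7 and the timeline which arm receives 60%.
- State whether members entering through inpatient-risk referral are included in the aggregate.

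The cost is one model term, using a randomisation date already held. No members or data are added.
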